Appendix 1. National Institutes of Health Stroke Scale (NIHSS)………………………..26-29

Appendix 2. Activities of daily living (ADL) questioner …………………………………30

Appendix 3. EQ-5D questioner …………………………………………………………31-32

**Background**

Stroke is one of the leading causes of death and disabilities in elderly population worldwide. In high-income countries, stroke is the third most common cause of death and the main cause of acquired adult disability [^1^](#_ENREF_1). The most widespread and widely recognized mutilation caused by stroke is motor impairment, although other cognitive functions may also be impaired ^[1-3](#_ENREF_1" \o "Langhorne, 2009 #1)^. Intensive functional therapy and rehabilitation programs are essential to minimize the cognitive and physical sequels associated with acquired brain injury, in order to maximize the patient's quality of life [^4^](#_ENREF_4)^,^ [^5^](#_ENREF_5). Unfortunately, these programs are only partially successful, and alternative approaches are needed to expand metabolic recovery of the injured cerebral tissues. Hyperbaric oxygen therapy (HBOT) has been proposed as a possible post-stroke adjuvant therapy. However, the results of HBOT application during the acute phase, i.e. immediately after stroke, are contradictory ^[6-9](#_ENREF_6" \o "Anderson, 1991 #331)^, whereas data on the effect of HBOT in the chronic stage are scanty.

HBOT has been investigated for treatment of numerous diseases for more than 300 years. The principal effect of HBOT is increasing the solubility of oxygen in plasma to a level sufficient to support tissues with minimal oxygen supply carried on by hemoglobin. Transport of oxygen to mitochondria, the main sites of oxygen utilization within each individual cell, occurs by diffusion, via a stepwise decrease in the driving oxygen pressure gradient. Diffusion oxygen gradient is a [vector](http://en.wikipedia.org/wiki/Vector_field)  indicating the direction of the greatest rate of change between oxygen dissolved in the blood and oxygen within the cell/entire tissue. As a whole, breathing oxygen under hyperbaric conditions has been shown to be a potent means of increasing arterial oxygen tension, as well as brain oxygen tension [^10^](#_ENREF_10)^,^ [^11^](#_ENREF_11) . For example, at 2 absolute atmospheres (ATA), plasma O_2_ tension rises above 1110 mmHg, whereas at normal environmental conditions, i.e. at the sea level, it reaches only 98 mmHg. As can be concluded, hyperbaric conditions can provide about a ten-fold increase in the amounts of O_2_ reaching the hypoxic brain tissue. HBO therapy is well tolerated and has been considered safe when used according to the standard protocols, with oxygen pressure not exceeding 3 ATA and treatment sessions limited to a maximum of 120 min [^12^](#_ENREF_12).

It has been speculated that following hypoxic/ischemic episodes, mitochondrial membrane alterations, microvascular failure and intermittent cerebral blood flow (CBF) reduction might impair efflux of oxygen from the capillaries into the tissue, and subsequently - into the neurons and then into the mitochondria, thus contributing to the functional failure of aerobic metabolism [^13^](#_ENREF_13) and development of oxygen delivery/demand mismatch. Increasing plasma oxygen concentrations by means of HBOT is a potent tool for urgent oxygen supply to the perfused tissue ^[14](#_ENREF_14" \o "Veltkamp, 2000 #9)^. Moreover, HBOT might augment oxygen delivery to the hypoxic brain areas by yet a different mechanism, namely via increasing deformability of the red blood cells [^15^](#_ENREF_15). Under normal conditions, HBOT application to the preserved, uninjured brain tissue also enhances brain oxygenation, albeit concomitantly induces vasoconstriction [^16^](#_ENREF_16). It has been demonstrated, both in experimental [^17-19^](#_ENREF_17) and clinical studies [^20^](#_ENREF_20)^,^ [^21^](#_ENREF_21), that CBF of injured brain does, indeed, decrease following exposure to HBOT. Furthermore, a propensity for vasoconstriction and decrease in CBF during exposure to HBOT was observed in uninjured areas of the brain, whereas in the injured areas CBF showed a tendency to increase ^[22](#_ENREF_22" \o "Bergo, 1993 #20)^. Therefore, it can be suggested that HBOT of the same magnitude differentially and selectively affects blood vessels within different brain areas, depending on the severity of the injury ^[22-24](#_ENREF_22" \o "Bergo, 1993 #20)^. It has been suggested that by such mechanism HBOT might initiate and/or regulate cellular and vascular repair processes within the injured brain [^7^](#_ENREF_7)^,^ [^25^](#_ENREF_25). Indeed, HBOT was shown to improve CBF in patients with chronic neurological deficiency, as demonstrated by brain SPECT imaging [^26^](#_ENREF_26)^,^ [^27^](#_ENREF_27).

The effects of HBOT on the damaged/ischemic neuronal tissue has been extensively evaluated [^28^](#_ENREF_28). Among the most important findings, the following should be mentioned: recovery of mitochondrial membranes and their functioning [^29-33^](#_ENREF_29); improved BBB and decreased secondary inflammatory reactions [^34^](#_ENREF_34)^,^ [^35^](#_ENREF_35); improved cellular metabolism [^7^](#_ENREF_7)^,^ [^26^](#_ENREF_26)^,^ [^35-38^](#_ENREF_35); initiation of anti-inflammatory activities, such as downregulation of ICAM-1 and other inflammatory cytokines [^28^](#_ENREF_28)^,^ [^35^](#_ENREF_35)^,^ [^39^](#_ENREF_39)^,^ [^40^](#_ENREF_40), diminished infiltration and reduced adhesion of leucocytes within the injured brain [^35^](#_ENREF_35)^,^ [^41-43^](#_ENREF_41); reduced COX-2 expression [^44^](#_ENREF_44), decreased synthesis of apoptosis-regulating proteins, e.g. caspase 3, caspase 9, bcl-2 and p53 and, accordingly, reduced apoptosis [^35^](#_ENREF_35)^,^ [^45^](#_ENREF_45)^,^ [^46^](#_ENREF_46); reduced expression of HIF-1 [^47^](#_ENREF_47)^,^ [^48^](#_ENREF_48); increased Na+-K+ ATPase activity and ATP production, resulting in stabilization of transmembrane ion gradients [^49^](#_ENREF_49); upregulation of antioxidant enzyme synthesis and reduction of hydroxyl radical formation [^50-53^](#_ENREF_50); suppression of NADPH oxidase [^54^](#_ENREF_54) activity; increased expression of neurotrophin [^44^](#_ENREF_44)^,^ [^55^](#_ENREF_55); increased NO activity [^56^](#_ENREF_56); inhibited Nogo-A, Ng-R, or RhoA expression [^57^](#_ENREF_57); up-regulated presence of axon guidance agents [^35^](#_ENREF_35) .

HBOT-associated neuronal effects can be also mediated indirectly, via glial cells and asrocytes ^[58](#_ENREF_58" \o "Gunther, 2005 #344)^. Glial cells, which are robustly activated after cerebral insult, are known to play important role in the processes associated with neuroprotection and/or neurodegeneration [^59^](#_ENREF_59)^,^ [^60^](#_ENREF_60). In a variety of pathologic conditions, including ischemia, microglial cells release soluble factors such as pro-inflammatory cytokines and proteases, which are directly linked to neurodegeneration [^61-63^](#_ENREF_61) By contrast, astrocyte activities promote the recovery of neuronal functions after injury by providing the energy substrates and trophic factors to btain cells, act as free radical and glutamate scavengers, promote remyelination and neovascularization and stimulate neurogenesis from neural stem cells [^64^](#_ENREF_64). In permanent cerebral ischemia, astrocytes might be involved in regulation of high-to-toxic ATP concentrations by the induced expression of specific P2X receptor subtypes ^[65](#_ENREF_65" \o "Franke, 2004 #356)^. In a model of permanent cerebral ischemia, HBOT has been demonstrated to decrease microgliosis, but to increase astrogliosis, within the peri-infarct areas ^[58](#_ENREF_58" \o "Gunther, 2005 #344)^. HBOT treatment has been shown to promote neurogenesis of the endogenous neural stem cells, thus also contributing to the repair processes within the injured brain ^[66-68](#_ENREF_66" \o "Wang, 2007 #369)^.

The major limitation, interfering with any conclusions drawn from the information concerning the metabolic effects of HBOT at the cellular level, is that these conclusions would be based on a striking diversity among the experimental models, types of neurologic damage and varieties of HBOT protocols (with respect to the applied pressure and duration of treatments). Nevertheless, there exists at least one underlying common denominator: unexceptionally, all described repair/regeneration mechanisms are energy/oxygen dependent. Consequently, at least one conclusion is unequivocal: HBO therapy improves metabolic processes of the neuronal tissue by providing the energy/oxygen supply, mandatory for successful regeneration processes within the brain recuperating from severe injury.

The improved metabolic platform generated by HBOT is expected to initiate and enable many regeneration processes. In other organs suffering from oxygen supply/ demand mismatch, such as non-healing wounds in diabetic patients, it was already prove that HBOT can initiate many regeneration process eventually culminate in wound healing. The same is expected to happen in the relatively hypoxic-energy depleted areas of the injured brain.

**Objectives**

The aim of the current study is to evaluate, for the first time in a prospective randomized study, the effect of hyperbaric oxygen therapy (HBOT) on patients with **chronic** neurological deficiency due to stroke.

- The primary endpoints of the study are to evaluate the effects of the HBOT on:
- National Institutes of Health Stroke Scale (NIHSS)
- Activities of daily living (ADL)
- Brain metabolism as visualized by SPECT
- The secondary endpoints included quality of life evaluation.

The safety of the HBOT in this post stroke population will also be evaluated and any adverse event will be recorded.

**Study design**

A prospective, randomized, control-crossed over trial.

The study will be done in the hyperbaric chamber and in the research and development unit of Assaf Harofeh Medical Center, Israel.

The brain SPECT evaluation will be done in Nuclear Medicine institute in Assaf-Harofeh Medical Center, Israel.

**Inclusion criteria**

- Ischemic or hemorrhagic stroke 6-36 months prior to the inclusion in the study.
- All patients had to have persistent (stable non improving) neurologic deficiency that includes at least one motor dysfunction (paresis or plegia) without noticeable improvement during the last month prior to their enrolment.
- age 18 years or older

**Exclusion criteria**

Patients will be excluded if they will have one of the following criteria:

- Dynamic neurologic improvement or worsening during the last month
- Had been treated with HBOT for any other reason prior to their inclusion
- Have any other indication for HBOT;
- Chest pathology incompatible with pressure changes;
- Inner ear disease;
- Patients suffering from claustrophobia;
- Inability to sign written informed consent.
- Smoking patients were not allowed to smoke during the study and if they could not comply with this demand they were excluded.
- Inability to sign informed consent

***Study protocol***

After signing the informed consent, patients were randomized in 1:1 manner into the treated or the control-cross group. After the randomization, patients were invited for baseline evaluation that included full review of their medical status and complete physical examination. All patients had baseline CT scan. After their inclusion patients were randomized to two groups: a treated group and a cross group. All patients had evaluation of their neurologic functions by physical examination, ability to perform activities of daily living, quality of life and brain functional imaging (rCBF-SPECT scan). The patients in the treated group were evaluated twice – at baseline and after 2 months of HBOT treatment. The patients of the cross group were evaluated three times – at baseline, after a 2 month control period of no treatment and after a consequent 2 month period of HBOT treatment. We emphasize that the study was a cross-over trial and patients in the cross group received HBOT treatment after their second evaluation and had a third neurological evaluation after the cross, when they have completed their HBOT.

The following HBOT treatment protocol was practice: The patient were treated 40 times (each treatment session was given on a separate day) distributed over two months (five days a week). Each session was for 90 minutes in 100% oxygen atmosphere and at pressure of 2 ATA.

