**Activities of daily living (ADL)**

The activities of daily living (ADL) will be evaluated by a questioner that covers the following functions: bathing, dressing, grooming, oral care, toileting, walking, climbing stairs, eating, shopping, cooking, managing medications, using phone, housework, doing laundry, driving and managing finances[^71^](#_ENREF_71). For each criterion the patient had to define whether he/she is independent, needs help, dependent or does not do at all (The range of the total score is from 0 (best) to 51 (worst)).

The ADL is attached in appendix 2.

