**Randomization**

Since the diversity of the patients included in the study, after signing the informed consent was expected to be high, no stratifies criteria was used. Patients were randomized in 1:1 fashion to either treatment or controlled-cross group.

There is no placebo in the cross group during the control period. The only way to give “placebo” of HBOT, is to bring the patients to the hyperbaric chamber and to increase the environmental pressure- in a way the patients will “feel the hyperbaric pressure” in their ears. However, Henry’s law states: “the amount of a given gas dissolved in a given type and volume of liquid is directly proportional to the pressure of that gas in equilibrium with that liquid”. Thus, hyperbaric environment significantly increases the dissolved oxygen pressure even if a person holding his breath[^76^](#_ENREF_76). Moreover, the alternative of hosting the patients in the hyperbaric chamber without any pressure increase cannot serve as a real placebo since the patients will not feel the pressure. Accordingly, the only real “placebo” could be archived by increasing the pressure and reducing the percentages of the oxygen but that holds significant safety consideration.

From the ethical point of view, it was deemed unethical to “treat” the patients (40 sessions in the hyperbaric chamber) while they actually know that it is a placebo. In order to somewhat compensate for this limitation, the control was a cross group and after the 2^nd^ evaluation at the end of a control period they were crossed to HBOT. The cross for treatment enables intra-group efficacy evaluation in both treatment and control group.

Since the patients knew they were not receiving HBOT during the control period they were not blinded with regard to the treatment arm. Accordingly the ADL and quality of life evaluations were not blinded. Moreover, in the current clinical setting, it was not possible to assure that the NIHSS evaluation could be done completely blinded by the physician. The complete blindness evaluation could be assured in the brain SPECT evaluation done by the radiologist. The correlation between metabolic blinded evaluation of the brain (SPECT) and the neurological un-blinded evaluations give further support and strength to the clinical findings.

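### The protocol places randomisation twice and inconsistently, and its only explicit order lets the baseline NIHSS and ADL be rated with the arm known

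*Protocol*

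**What the plan says.** The Study protocol section describes the start of the trial in one paragraph. First: "After signing the informed consent, patients were randomized in 1:1 manner into the treated or the control-cross group". Next: "After the randomization, patients were invited for baseline evaluation that included full review of their medical status and complete physical examination". After a sentence on the baseline CT scan it adds: "After their inclusion patients were randomized to two groups: a treated group and a cross group". The Randomization section repeats the 1:1 allocation ("Patients were randomized in 1:1 fashion to either treatment or controlled-cross group") without saying when it happens relative to baseline or whether it is concealed until then.

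That section also explains that the control period has no placebo. On patients it says "they were not blinded with regard to the treatment arm". On outcomes it says "Accordingly the ADL and quality of life evaluations were not blinded", and for NIHSS that "it was not possible to assure that the NIHSS evaluation could be done completely blinded by the physician". Only the SPECT reading is described as assured blind.

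ADL is the patient's own answer, item by item: "For each criterion the patient had to define whether he/she is independent, needs help, dependent or does not do at all". NIHSS and ADL are the co-primary endpoints (Primary Efficacy Analysis Set; Primary Efficacy Analysis), and Sample Size Considerations sets a 25% improvement relative to the pre-treatment baseline as the clinical target.

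**The concern.** A trial without a sham cannot keep patients blind once treatment starts. It can keep the baseline blind, because before allocation neither patient nor rater can know the arm. Under the explicit order in the Study protocol section, that protection is lost. A patient who already knows the arm may answer the ADL items differently, and a physician who knows it may score borderline NIHSS items differently. Since both co-primary outcomes are changes from that baseline, a shift there passes directly into apparent improvement or apparent lack of it.

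The order also affects who is counted. The medical review and examination follow allocation, so anyone who fails to attend or is found unsuitable at that visit has already been randomised. The Primary Efficacy Analysis Set keeps only patients who finish their period with valid scores and without major violations, so such patients would drop out of the comparison.

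**Working it through.** **1. The statements side by side.**

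- First statement: consent, then randomisation, then invitation to the baseline evaluation. The order is explicit.
- Second statement: randomisation after inclusion. It stands after the sentences on medical review, examination and CT, but inclusion is not tied to any visit or assessment.
- Randomization section: no timing, and no step that conceals the arm until baseline is complete.

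The two placements cannot both describe one randomisation unless inclusion means no more than signing consent. If inclusion means passing the medical review, they contradict each other. The protocol does not say which is meant.

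**2. Exposure of each baseline measure under the explicit order.**

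- ADL: self-reported and stated to be not blinded, so it can be scored with the arm known.
- NIHSS: physician-rated, with complete blinding not assured. This is weaker than saying it is unblinded.
- SPECT: graded by blinded readers.

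**3. Illustration of size.** The protocol gives no baseline NIHSS or ADL values, so the true scores below are assumptions. The calculation also reads the 25% as a per-patient change in score. On both scales a higher score is worse. Suppose the true score b does not change over two months and baseline is over-rated by s points. The recorded baseline is b + s, follow-up is b, and the apparent improvement is s/(b + s).

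| True score b | Recorded baseline (s = 1) | Apparent improvement 1/(b + 1) |
|---|---|---|
| 3 | 4 | 1/4 = 25% |
| 4 | 5 | 1/5 = 20% |
| 8 | 9 | 1/9 = 11% |
| 12 | 13 | 1/13 = 8% |
| 20 | 21 | 1/21 = 5% |

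Reaching 25% needs s/(b + s) ≥ 0.25, that is s ≥ b/3: 2 points at b = 4 (2/6 = 33%), 3 at b = 8 (3/11 = 27%), 4 at b = 12 (4/16 = 25%) and 7 at b = 20 (7/27 = 26%). ADL runs to 51, so where ADL scores are high one point matters little and a shift over several items would be needed.

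The opposite shift works the other way. A true 8 recorded as 7 at baseline and 8 at follow-up appears as a worsening of 1/7 = 14%.

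**4. Why adjustment does not help.** Let the baseline in one arm be recorded s points too high, and let the slope of follow-up on recorded baseline be β. A change score carries the full bias s. Covariate adjustment carries β × s. Adjustment shrinks the error when β is below 1 but removes it only if β = 0, that is, if baseline predicts nothing.

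**5. Sample size.** The stated N of 31 does not depend on the timing of randomisation, so this point leaves it unchanged.

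**The case against.** The strongest reply is that the second randomisation sentence follows the medical review and CT and speaks of patients already included, so randomisation may really have come after baseline. That is possible, and it is why a flat claim that patients were randomised before baseline goes too far. It does not settle the matter: the only sentence that explicitly orders the two steps puts randomisation first.

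Several stronger inferences are tempting and are not supported:

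- *That patients and raters knew the arm at baseline.* The protocol says patients knew they were untreated during the control period. Knowledge at the baseline visit is inferred from early randomisation, the open design and the absence of a concealment step.
- *That exclusions depended on the arm.* No passage says the exclusion criteria are judged at the baseline visit, and several could be checked at consent. Only the conditional holds: losses at that visit would be post-randomisation losses.
- *That the bias favours HBOT.* Controls waiting for treatment might also rate themselves worse. The direction is unknown.
- *That one point meets the target at any score up to 4.* At a true 4 it gives 20%. It reaches 25% only at a true score of 3 or less.

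It is also fair to say that the 25% is not clearly a per-patient change. Primary Efficacy Analysis treats 0.25 and 0.04 as proportions of success. On that reading the shift acts through whatever defines an individual success, and no size can be given.

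Finally, follow-up ratings stay open. With a correct baseline of 8, one point under-rated at follow-up gives 1/8 = 12.5%. The Randomization section acknowledges the general lack of blinding. That acknowledgement concerns the missing sham and does not address baseline timing, where blinding costs almost nothing.

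**Conclusion.** The concern stands in this form: the Study protocol section states the randomisation step twice and inconsistently, and its one explicit order allows the baseline NIHSS and ADL to be rated with the arm known. This rests on the text itself and on the absence of any concealment step. Whether the arm was in fact known, whether anyone was lost at that visit, and which way ratings would move are not established.

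The size is illustrative only. Under the per-patient reading, a one-point over-rating ranges from the whole 25% target at a true score of 3 to about a fifth of it (5 of 25 percentage points) at 20. It is a defect worth correcting because it touches the reference value of both co-primary outcomes, cannot be repaired in the analysis, and is avoidable.

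**What to change.** Reconcile the Study protocol section to a single order:

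1. informed consent;
2. eligibility review;
3. baseline NIHSS, ADL, EQ-5D and SPECT recorded and locked;
4. randomisation, with the allocation revealed only then.

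Delete the conflicting randomisation sentence, and state the same timing in the Randomization section.

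The cost is wording plus a small logistical burden: allocation must wait until all baseline assessments are complete, including SPECT, which is done in the hospital's nuclear medicine institute. The sample size does not change.

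The change has limits. It does not remove bias from open NIHSS and ADL ratings at follow-up. Nor does it protect the cross group's second evaluation, which is that group's reference before HBOT and necessarily comes after allocation. The Randomization section acknowledges part of this, and those limits should stay stated.
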